#### Exercise adjustments in case of pain

If a participant experienced incidence of joint pain or the like during a specific exercise, we asked them to adjust the exercise as follows: First, the instructor asked the participant to externally rotate the arms, slightly alter the path of the arms or reduce the range of movement during the exercise. Then, the participant reduced the training load of the exercise (e.g. a reduction of 1 kg). If this did not help, the participant reduced the number of sets, and finally reduced training frequency. If none of these adjustments had the desired effect, the exercise was removed from the participant's training program for at least 1 week.

#### Motivation

Compliance to training is challenging. Workplace interventions have typically reported low to moderate compliance [23,24]. In the VIMS-study, we focused especially on the environment. We tried to improve compliance by placing the training facilities close to working offices to reduce transportation time and distance as a barrier for not training. Whenever possible, we chose bright rooms and made efforts to make the rooms appealing. We ensured sufficient space to move freely. Colored posters illustrating the exercises with instructions were hung on the walls. The participants received a training diary for registering training sessions and loads. We encouraged participants to train during a specified time period together with their colleagues. Instructors supervised half of the training sessions in groups 1WS, 3WS and 9WS. Instructors taught the participants how to perform the exercises, and helped with exercise adjustment when needed. The instructors focused on positive feedback to maintain motivation. The instructors met regularly to discuss positive and negative experiences and possible problems. A mail-support was created for the participants in case of questions or problems regarding the exercises.

### Self-reported measures

We applied a structured email-based questionnaire including e.g. the Standardized Nordic questionnaire for musculoskeletal disorders [25], the International Physical Activity Questionnaire (IPAQ) [26], self-efficacy [27,28], stages of change [28-32], and work productivity [33]. The main questions are described in more detail below.

*Musculoskeletal pain symptoms *of the neck, shoulder, arm, hand, and back were evaluated using validated scales concerning both intensity and duration of symptoms. Participants replied to the questions "How many days have you had trouble in [body part] during the last three months?" (0 days; 1-7 days; 8-30 days; >30 days; everyday) for symptom duration, and "On average, how intense was your pain in [body part] during the last three months on a 0-9 scale?" (where 0 means no complaints and 9 means pain as bad as it can be) for symptom intensity. Answers to the question that concerned symptom duration were recoded as follows: 0 days = 0, 1-7 days = 4, 8-30 days = 19, >30 days = 60, everyday = 90. Illustrations from the Nordic questionnaire defined the respective body regions [25]. Further, headache was evaluated using a questionnaire on intensity, duration, and frequency of headache during the previous month.

*The level of physical activity *were assessed using the International Physical Activity Questionnaire (IPAQ) [26]. Total physical activity and vigorous-intensity activity during work, transportation, housework or gardening, and leisure were converted to metabolic equivalent task (MET minutes per week) according to the guidelines for data processing of the IPAQ. Also, participants were classified into the High, Moderate, or Low category based on their level of activity. Participants in High performed on a weekly basis: a) vigorous-intensity activity on at least 3 days, achieving a minimum of 1500 MET minutes per week; or b) different activities 5 or more days achieving a minimum of 3000 MET minutes per week. Participants in Moderate performed: a) 3 or more days of per week of vigorous-intensity activity of at least 20 min per day; or b) 5 or more days per week of moderate-intensity activity or walking of at least 30 minutes per day; or c) 5 or more days of different activities achieving a minimum of 600 MET minutes per week. Participants who did not meet the criteria for the two other categories were placed in the Low category.

*Self-efficacy *in relation to barriers towards physical activity was assessed by a questionnaire [27,28]. E.g. "I feel convinced that I am able to exercise 3 times or more a week with a duration of at least 20 minutes at a time even though: "I am under a lot of stress", "I feel I don't have the time", "I have to exercise alone", "I don't have access to exercise equipment", "I am spending time with friends or family who do not exercise", and "It's raining or snowing".

*Stages of change *in relation to physical activity was in this study assessed by a questionnaire originally presented by Marcus and colleagues in 1992 [27] but further developed by Benisovich in 1998 [28-32]. Questions asked in the questionnaire were e.g. "As far as I'm concerned, I don't need to exercise regularly", "I really think I should work on getting started with a regular exercise program in the next 6 months", and "I have started exercising regularly within the last 6 months".

*Productivity *was rated on an 11-step ordinal scale: "How do you perceive your overall productivity the last 4 weeks?" The rating went from 0 (the worst a worker could do) to 10 (the best a worker in the same job could do) [33]

### Objective measures

Testing of physical capacity was performed at the beginning, midways, and at the end of the 20-week intervention in all five groups.

*Maximal muscle strength *was assessed by a repetition maximum (RM) test at baseline, at midterm (10 weeks) and at the end of the intervention (20 weeks). We used the bilateral lateral raise exercise (i.e. from neutral position to 90 abduction/30 horizontal flexion). The participant stood with the back against a wall, and performed 1 repetition with 1 kg dumbbells and held the top-position for 1-2 seconds, waited 30 seconds, and then one repetition with 2 kg dumbbells. Using this procedure, the examiner added 1 kg until the participant was unable to lift and hold the dumbbell properly. The maximal weight lifted with acceptable technique was noted as 1 RM.

*Strength-endurance *was assessed with a submaximal load. Using the same exercise as described above, the participant performed as many repetitions as possible with a load of 1 kg less than the 1 RM load. During each repetition the participant held the top-position for 1 second. The participant used the same load during midterm and end of intervention as the one used during the baseline test.

### Statistics

The primary outcome is change in pain of the neck and shoulders at 20 weeks. Secondary outcomes include the other measures mentioned above. We plan to analyze the main data according to the intention-to-treat principle. Secondly, we will also analyze data per protocol. We will use repeated measures analysis of variance. Our design allows us to compare both the effect of different combination of duration and frequency and the effect of training supervision (figure 3). The following null-hypotheses will be tested;

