**Figure 1 F1:**
[figure not shown]
**Flow-chart**. 1WS: one weekly session with supervision, 3WS: 3 weekly sessions with supervision, 9WS: 9 weekly sessions with supervision, 3MS: 3 weekly sessions with minimal supervision. Reference: reference group without training

Exclusion criteria were (i) hypertension (Systolic BP >160, diastolic BP > 100) or cardiovascular diseases, (ii) symptomatic herniated disc or severe disorders of the cervical spine, (iii) postoperative conditions in the neck and shoulder region, (iv) history of severe trauma, and (v) pregnancy, (vi) or other serious disease. Prospective participants had to work at least half of their working hours in an office environment to be included. The remaining 573 participants were randomly allocated at the cluster level to five groups as described below. Table 2 shows the baseline characteristics of the included participants of the five groups. After the cluster randomization, workers were excluded if they contracted a condition included in the aforementioned exclusion criteria or if they were on maternity leave or on other long-term absences (men and women).

**Table 2 T2:** Characteristics of the five groups.

	1WS (N = 115)	3WS (N = 122)	9WS (N = 113)	3MS (N = 126)	Reference (N = 97)
Age (years)	47 (11)	47 (11)	46 (10)	45 (11)	46 (10)
Height (cm)	174 (9)	174 (10)	175 (9)	175 (10)	175 (10)
Weight (kg)	77 (15)	76 (18)	77(14)	78 (16)	80 (16)
BMI (kg^.^m^-2^)	25 (4)	25 (4)	25 (4)	26 (4)	26 (5)
Neck pain intensity previous 3 months (scale 0-9)	3.3 (2.2)	3.2 (2.4)	3.1 (2.3)	3.3 (2.3)	3.2 (2.3)
Shoulder (right) pain intensity previous 3 months (scale 0-9)	2.2 (2.3)	2.3 (2.4)	1.9 (2.2)	2.0 (2.4)	2.0 (2.3)
Shoulder (left) pain intensity previous 3 months (scale 0-9)	1.5 (2.1)	1.7 (2.2)	1.8 (2.2)	1.6 (2.2)	1.4 (1.8)
12-month prevalence of neck pain	89%	89%	88%	92%	90%
12-month prevalence of right shoulder pain	69%	69%	63%	66%	62%
12-month prevalence of left shoulder pain	54%	58%	59%	56%	53%

1WS: one weekly session with supervision, 3WS: 3 weekly sessions with supervision, 9WS: 9 weekly sessions with supervision, 3MS: 3 weekly sessions with minimal supervision. Reference: Reference group without training

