**Figure 3 F3:**
[figure not shown]
**Schematic illustration of the four training groups**. Using this design we can compare the effectiveness of both time-wise combinations of training and the influence of training supervision.

1) There is no difference between the groups 1WS, 3WS, 9WS and reference for the change in neck/shoulder pain from baseline to week 20.

2) There is no difference between the groups 3WS, 3MS and reference for the change in neck/shoulder pain from baseline to week 20.

Power analyses performed prior to the study showed that - to reject the null-hypothesis of equality - we should include 150 participants per group (allowing for a 20% loss to follow-up) for 80% power to detect a 10% change in pain between groups.

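### The stated primary analysis compares change from baseline with no baseline covariate named; adjusting for baseline pain would be more precise, at little cost, in a trial that randomised 573 rather than 750

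*Protocol article*

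**What the plan says.** The Statistics section of the protocol article defines the endpoint as a change: "The primary outcome is change in pain of the neck and shoulders at 20 weeks". The method takes one sentence: "We will use repeated measures analysis of variance". The two null hypotheses, listed after Figure 3 in the same section, are both on the change scale. The second reads "There is no difference between the groups 3WS, 3MS and reference for the change in neck/shoulder pain from baseline to week 20", and the first compares 1WS, 3WS, 9WS and reference in the same terms. No covariate is named and none is ruled out.

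On size, the article says "we should include 150 participants per group". That number already allows for one participant in five being lost, and its purpose is given as "for 80% power to detect a 10% change in pain between groups". The Study population section then reports the number actually allocated: "The remaining 573 participants were randomly allocated at the cluster level to five groups as described below". Table 2 gives groups of 115, 122, 113, 126 and 97, and tabulates baseline pain intensity for all five.

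**The concern.** Outcome, hypotheses and method all point to one test. When baseline and week 20 are the two occasions of a repeated measures analysis of variance, the group-by-time test is the comparison of mean change scores between groups. A change score subtracts the whole baseline value, which is the best use of baseline only if baseline predicts week 20 perfectly. For a self-rated 0-9 pain score with SD about 2.3 it will not, so part of the baseline noise is added to the outcome.

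Analysing week-20 pain, or change, with baseline as a covariate targets the same group difference with a smaller standard error. Every group fell below the 150 planned, and the reference group, which enters both hypotheses, is the smallest at 97. Precision given up in the analysis is therefore precision that the trial has reason to want.

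**Working it through.** **The plan's own figure.** The 150 per group cannot be reproduced from the article, because the SD, the significance level and the base of the 10% are not given. Taking two-sided 0.05 and 10% as 0.9 points on the 0-9 scale, and dividing by 0.8 for loss:

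- SD 2.3 (typical of Table 2) gives 103, inflated to 129.
- SD 2.47 gives 119, inflated to 149.
- SD 2.5 gives 122, inflated to 153.

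So 150 fits if an SD of about 2.5 was used. Taking 10% of the baseline mean (about 0.32 points, SD 2.3) gives 811, inflated to 1,014, which does not fit.

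**Shortfall.** 115 + 122 + 113 + 126 + 97 = 573. Planned: 5 × 150 = 750. 573/750 = 76%.

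**Variance.** Let s be the SD at each occasion (taken as equal) and r the correlation between baseline and week 20.

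- Change score: variance 2(1 − r)s².
- Baseline-adjusted: variance (1 − r²)s².
- Ratio, adjusted to change: (1 − r²) / [2(1 − r)] = (1 + r)/2, which is below 1 whenever r is below 1.

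**Power anchored to the plan's own target.** This avoids choosing an SD or a base for the 10%. It assumes that the 150 was calculated for an unadjusted two-group comparison at two-sided 0.05.

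- Evaluable per group as planned: 150 × 0.8 = 120.
- Standardised effect giving 80% power: (1.960 + 0.842)/√(120/2) = 0.362.
- 9WS versus reference after 20% loss: 113 × 0.8 = 90.4 and 97 × 0.8 = 77.6.
- Unadjusted: 0.362/√(1/90.4 + 1/77.6) = 2.34, so power is Φ(2.34 − 1.96) = about 65%.
- Adjusted: divide 2.34 by √[(1 + r)/2]. At r = 0.5 this is 2.34 × √(4/3) = 2.70, so power is about 77%.

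| r (assumed) | Variance ratio | Equivalent extra participants | Adjusted power (unadjusted 65%) |
|---|---|---|---|
| 0.4 | 0.70 | 43% | 80% |
| 0.5 | 0.75 | 33% | 77% |
| 0.7 | 0.85 | 18% | 72% |
| 0.8 | 0.90 | 11% | 69% |

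**A second anchor.** Fix SD at 2.3 and the effect at 0.9 points, and take 3WS versus reference (97.6 and 77.6 evaluable). Power, change score against adjusted, is 73.0% and 84.4% at r = 0.5, 91.3% and 95.0% at r = 0.7, and 98.2% and 99.0% at r = 0.8. With an assumed intracluster correlation of 0.05 and about 7 completers per cluster (573 × 0.8/65), the pair at r = 0.5 falls to 61.6% and 74.0%.

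**Baseline imbalance.** In Table 2, mean neck pain is 3.1 to 3.3 across the groups, at most 0.1 from reference. The part of a baseline difference d that a change score carries into the estimate is (1 − r)d in size, so at r = 0.5 this is 0.05 points. The largest shoulder difference from reference is left shoulder in 9WS, 1.8 against 1.4, which carries 0.2 points.

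**The case against.** The strongest reply is that the article names a family of methods in one sentence and is silent on covariates, which a condensed article commonly leaves to the full analysis plan. A change outcome can be analysed with baseline as a covariate, and then gives the same group difference as adjusted week-20 pain. The abstract also words the main outcome as pain at week 20 rather than as change. This stands to the extent that a reader might infer that baseline adjustment has been rejected; the article does not say so. It does not remove the point, because the change outcome, the change hypotheses and the named method together state an unadjusted comparison, and the abstract's wording specifies no adjustment either.

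A reader might also infer that the planned test is biased or wrong. It is not: under randomisation a comparison of change scores is valid and unbiased, and what is lost is efficiency. Nor does regression to the mean give an argument of any weight, since 65 clusters were randomised within strata and the imbalance in Table 2 is small.

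Finally, a reader might infer that adjustment would recover most of the lost power. That depends on r, which is not given. On the first anchor, 9WS versus reference loses about 15 points (80% to 65%); adjustment returns about 12 of them at r = 0.5 but only about 4 at r = 0.8. On the second anchor the gain at r = 0.8 is under 1 point. Both anchors use a single pairwise contrast, whereas the stated hypotheses cover four and three groups.

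**Conclusion.** The point holds as one of efficiency. The primary analysis as written is a comparison of raw change scores, and a baseline-adjusted analysis of data already collected is more precise for any r below 1. The variance reduction is (1 − r)/2: 30% at r = 0.4, 25% at 0.5, 15% at 0.7 and 10% at 0.8. In power for 9WS versus reference, that is a rise from about 65% to between 69% and 80% over that range.

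The variance ratio rests on equal variances at the two occasions and on baseline and week 20 being the two occasions analysed. The power figures rest further on two-sided 0.05, 20% loss, no allowance for clustering, and the 150 having been calculated for an unadjusted comparison. The direction of the gain is secure; its size is not, because the article gives no r.

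**What to change.** In the Statistics section, state the primary analysis as week-20 pain intensity (or change in it) with baseline pain intensity as a covariate, or as a baseline-constrained mixed model. Put the stratum and cluster terms in the same model, and report adjusted group differences. Unadjusted change can stay as a descriptive display. If the full analysis plan already includes baseline as a covariate, one line saying so is enough.

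The cost is small: one or two sentences and one covariate already collected, with no new data. The wording should be fixed before outcome data are analysed, so that the choice of adjustment cannot depend on the results.

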### Procedure of the cluster randomization

Work place physical exercise has implicit social elements of both getting together, competition and group pressure. For the intervention to capture these elements, we used cluster as the unit of randomization. The clusters were naturally occurring groups of employees, thereby also minimizing contamination between clusters. To help ensure the comparability of the 4 intervention groups and the reference group, geographical sites were categorized into 13 strata. Each stratum was divided into 5 naturally occurring clusters. Building, floor, department and the size of clusters were taken into account when defining the clusters in order to attain intervention and reference groups of similar sizes in each stratum. Strata and clusters were formed by authors MZ, LA and GS. In two of the strata forming of clusters entailed individual randomization into two clusters. This individual randomization was performed by a data manger when stratum and cluster affiliation was attached to the participants.

Within each stratum the clusters were randomized to group (group was sampled with replacement and assigned to the cluster). Randomization was performed by author HF using a SAS macro based on the RANUNI function. In more details: Strata were numbered consecutively (1,...,13) and clusters numbered consecutively with strata (1,...,5). Within each stratum, the clusters were sorted according to a random number and assigned the color codes red, green, blue yellow white (a code for the 4 interventions and the reference group) in succession and cyclically. To minimize imbalance over several strata with a number of clusters no divisible by five, the SAS macro was programmed to start the cyclic assignment by assigning one of the colors at random (with probability 1/5). As the formation of clusters resulted in exactly five clusters in each stratum, this element of the macro was redundant.

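### The only analysis named, a repeated measures ANOVA, has no stated term for the 65 randomised clusters or the 13 strata; if clusters are ignored, type I error exceeds 5% at any positive ICC

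*Protocol article*

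**What the plan says.** Design. The section on the procedure of the cluster randomization states that "we used cluster as the unit of randomization". It also states that "geographical sites were categorized into 13 strata" and that "Each stratum was divided into 5 naturally occurring clusters". The reason for clustering is given there too: "Work place physical exercise has implicit social elements of both getting together, competition and group pressure". Under Study population the article adds: "The remaining 573 participants were randomly allocated at the cluster level to five groups as described below".

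Analysis. The Statistics section defines the outcome ("The primary outcome is change in pain of the neck and shoulders at 20 weeks") and names one method: "We will use repeated measures analysis of variance". It adds intention-to-treat first and per protocol second. The two null hypotheses concern change from baseline to week 20. One compares four groups (1WS, 3WS, 9WS, reference) and the other three (3WS, 3MS, reference). No cluster effect, stratum effect, robust variance or ICC is mentioned. The sample size statement asks for 150 participants per group, and the only allowance it names is for 20% loss.

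Allocation wording. The randomization section summarises the draw as "group was sampled with replacement and assigned to the cluster". Its detailed account then sorts the clusters of a stratum at random and gives them the five colour codes in turn, with exactly five clusters in every stratum.

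**The concern.** The article says it chose clusters because social effects act within them. That is a reason to expect people in the same cluster to change alike. A repeated measures ANOVA, as named, deals with the correlation between measurements on one person and not with the correlation between people randomised together. If the test compares 573 people as though each had been allocated separately, positive correlation of change within clusters makes the standard error of every arm comparison too small. Both primary hypotheses would then be rejected too often when true.

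Omitting the strata works in the other direction. Between-stratum variation stays in the residual, so the precision that stratified allocation could provide is lost.

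**Working it through.** **Inputs from the article.** 13 strata × 5 clusters = 65 clusters, 13 per group. Participants: 115 + 122 + 113 + 126 + 97 = 573. Mean cluster size m = 573/65 = 8.8.

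**Assumed.** The ICC of change in pain is not given; the range 0.01 to 0.10 is used. Two-sided 5% is assumed, because no significance level is stated.

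**The plan's own figure.** 150 per group less 20% leaves 120. The 150 cannot be reproduced, because the significance level, the SD and the base of the 10% change are not given. It therefore cannot be shown whether clustering was allowed for. If it was not, the need would be 150 × DE.

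**Pairwise test with clusters ignored.** DE = 1 + (m − 1) × ICC. The standard error should be multiplied by √DE. True error = 2 × [1 − Φ(1.96/√DE)]. Example at ICC 0.05: DE = 1 + 7.82 × 0.05 = 1.39, √DE = 1.18, and the true error is 9.7%.

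| Assumed ICC | DE | √DE | True error, m = 8.8 | True error after 20% loss, m = 7.05 | 150 × DE |
|---|---|---|---|---|---|
| 0 | 1.00 | 1.00 | 5.0% | 5.0% | 150 |
| 0.01 | 1.08 | 1.04 | 5.9% | 5.7% | 162 |
| 0.02 | 1.16 | 1.08 | 6.8% | 6.4% | 174 |
| 0.05 | 1.39 | 1.18 | 9.7% | 8.6% | 209 |
| 0.10 | 1.78 | 1.34 | 14.2% | 12.2% | 268 |

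**Four-group test of hypothesis 1.** This was simulated under the null with 13 clusters per arm and 4000 runs per setting.

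| Assumed ICC | Clusters ignored: 20% loss, cluster-size CV about 0.5 (assumed) | Clusters ignored: equal clusters of 9, no loss | Cluster-mean test blocked on stratum (both set-ups) |
|---|---|---|---|
| 0.02 | 7.9% | 8.2% | 4.1%, 5.1% |
| 0.05 | 13.0% | 12.2% | 4.7%, 4.5% |
| 0.10 | 22.3% | 23.9% | 5.3%, 5.5% |

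With equal clusters of 9, the three-group test of hypothesis 2 gave about 7%, 12% and 19% at the same ICCs. At ICC 0 the four-group test gave 5.0%.

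**Strata.** With a stratum effect of 0.05 and no cluster effect, the four-group test that ignored both rejected in 3.9% of runs. Leaving out stratum is thus mildly conservative.

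**Which model repairs it.** The hypotheses concern change. Write pain at time t as group-by-time means + cluster intercept + participant intercept + error. Subtracting baseline from week 20 removes both intercepts and any stratum main effect. What remains is the group difference in change plus error, so correlation of change within clusters is still unmodelled. In a simulated example the group × time standard error was 0.1353 with these random intercepts and also 0.1353 with clusters ignored. With a random cluster effect on change it was 0.1686, a ratio of 0.1686/0.1353 = 1.25.

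**The case against.** The strongest objection is that the article does not say the ANOVA is at individual level or that clusters will be ignored. A reader might infer both, and might go on to say that the p-values and intervals will certainly be wrong. The text does not support that. It names a method without unit, error terms or covariates. A repeated measures ANOVA can carry cluster as a random factor and stratum as a block, and an analysis plan that is not shown may do so. The harm also needs a positive ICC of change, and none is given. At 0.01 it is small, and the large figures rest on an assumed 0.05 to 0.10.

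This makes the point conditional but does not remove it. The article fixes a method and two hypotheses, describes the allocation down to the software function, and gives its own reason to expect correlation within clusters. None of that structure reaches the named analysis or the stated allowance in the sample size. Followed as written, the method does not fit the design.

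A second tempting inference is that drawing groups with replacement left strata without all five groups. The detailed algorithm in the same section rules this out: five codes are given in turn to exactly five clusters. That is a wording slip, and each stratum is a complete block.

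**Conclusion.** The concern holds in conditional form. The plan randomises 65 clusters in 13 strata and names an analysis with no provision for either. If clusters are ignored, the standard error is too small by about 4% at ICC 0.01 (1 − 1/1.04) to about 25% at ICC 0.10 (1 − 1/1.34). The resulting error rates run from negligible excess to several times the nominal 5%, and the multi-group primary tests are hit harder than single pairwise comparisons. The result rests on three assumptions: that clusters are left out of the model, that the ICC of change is above zero, and that cluster sizes are near the mean of 8.8. Because the validity of both primary tests depends on it, it should be settled before the data are analysed.

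**What to change.** In the Statistics section, state that the primary test accounts for cluster at the level of change. Any one of these will do:

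- a linear mixed model on change, or on week-20 pain adjusted for baseline pain, with a random effect for cluster and stratum as a factor;
- if both time points are modelled, random cluster and cluster-by-time effects, with stratum-by-time;
- an analysis of cluster means of change, blocked on stratum.

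Use small-sample degrees of freedom for the mixed models. The blocked four-group cluster-mean test has (13 − 1) × (4 − 1) = 36 residual degrees of freedom. Do not rely on random intercepts for cluster and participant alone.

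Report the ICC of change. State which cluster each of the 43 re-allocated participants belongs to in the analysis, because the section on the sequel to the randomization settled some of these by coin or by preferring no change of group. As a minor correction, bring the summary phrase on replacement into line with the detailed algorithm: five groups to five clusters, without replacement.

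The cost is a few sentences and a few lines of code. Stratum and cluster labels were attached to participants at randomization, so no new data are needed beyond settling the re-allocated cases. Confidence intervals will be somewhat wider.

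### Repeated measures ANOVA in its classical form drops everyone without a week-20 pain score, which does not fit the planned intention-to-treat analysis; the plan should name a model form that keeps them

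*Protocol article*

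**What the plan says.** All statements are in the Statistics section of the protocol article.

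- Outcome: "The primary outcome is change in pain of the neck and shoulders at 20 weeks". Both null hypotheses compare groups on the change between baseline and week 20.
- Principle: "We plan to analyze the main data according to the intention-to-treat principle". A second analysis follows: "Secondly, we will also analyze data per protocol".
- Method: "We will use repeated measures analysis of variance". The article gives no estimation method, covariance structure or software procedure.
- Expected loss: the sample size of 150 per group was set "allowing for a 20% loss to follow-up", and "for 80% power to detect a 10% change in pain between groups".

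The Study population section reports 573 randomised participants. Table 2 gives the group sizes as 115, 122, 113, 126 and 97.

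**The concern.** The article makes two commitments that may not fit together. Intention to treat calls for an analysis of everyone randomised. Repeated measures ANOVA in its classical form uses only people who have every score in the model. The plan itself allows for a fifth of participants being lost, so the gap is not trivial.

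Loss could plausibly differ between groups. The Motivation section calls adherence a challenge, and the section on exercise adjustments anticipates pain during training. The intervention section gives the reference group no training, only questionnaires. If the people lost differ in pain from those retained, and do so differently by group, then both the training-versus-reference contrasts and the contrasts between schedules are estimated in self-selected subsets.

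The objection is to the method that the article names. It is not an objection to the lack of a missing-data section, which an article may leave to the analysis plan.

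**Working it through.** **1. The plan's own figure.** 150 x 0.80 = 120, and 120 / 0.80 = 150, so the allowance corresponds to 120 participants per group with data. The article states neither an SD nor an alpha, so 150 cannot be reproduced from its inputs alone. Assume two-sided alpha 0.05 and n = 2(1.96 + 0.84)² SD² / δ².
- Reading 10% as 0.9 points of the 0-9 scale, SD 2.5 gives n = 122, and 122 / 0.80 = 153, close to 150.
- Reading it as 10% of mean baseline neck pain (about 0.32 points), SD 2.3 gives n = 811, and 811 / 0.80 = 1,014.

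So 0.9 points is the better yardstick for the target difference.

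**2. Who contributes under the classical form.** With two time points, the group-by-time test equals a one-way ANOVA on D = Y20 − Y0. D does not exist when Y20 is missing. At 20% loss:
- left out: 0.20 x 573 = 114.6, about 115
- analysed: 0.80 x (115, 122, 113, 126, 97) = about 92, 98, 90, 101 and 78, or 458.4 before rounding.

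**3. When unadjusted change in completers is biased.** Suppose loss depends only on baseline pain, and the SD is the same at both times with correlation ρ between them. Within a group,

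bias in mean change = (ρ − 1) x (completers' baseline mean − full-group baseline mean),

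and the second bracket equals −(loss fraction) x (lost mean − retained mean).

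Illustration (assumptions): 20% loss in each arm, random in the reference group. Among trainees the log-odds of loss rise by 0.5 to 1.0 per SD of baseline pain. SD is 2.3 (Table 2 shows 2.2 to 2.4) and ρ is 0.4 to 0.6. Lost trainees then have baseline pain 1.11 to 1.99 points above retained trainees, and completers' baseline falls by 0.20 x 1.11 = 0.22 to 0.20 x 1.99 = 0.40 points.
- Smallest bias: (0.6 − 1) x (−0.22) = +0.09
- Largest bias: (0.4 − 1) x (−0.40) = +0.24

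A true effect of −0.90 would appear as about −0.81 to −0.66. Simulation of the same setting gave −0.82 to −0.67, while an estimate conditioned on baseline stayed at −0.89 to −0.91. Here the bias runs against training. If low-pain trainees were the ones lost, the sign would reverse. If both arms lost people by the same mechanism and at the same rate, the biases would cancel.

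**4. A setting where completers do no harm.** In another simulation (about 20% loss, related to week-10 pain among trainees only, equal correlations of 0.6, true effect −0.90), the completers' contrast was −0.90. With equal variances and correlations, Cov(Y20 − Y0, Y10) = 0, so selection on week-10 pain leaves mean change intact. A likelihood estimate from baseline and week 20 alone gave −1.01. One that also used week 10 gave −0.90.

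**5. Loss related to the unseen outcome.** If lost trainees' unobserved week-20 pain were 0.5 to 1.5 points worse than a missing-at-random model predicts (assumption), the trainee mean would shift by 0.20 x 0.5 = 0.10 to 0.20 x 1.5 = 0.30 points. A delta-shifted analysis displays this quantity.

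**The case against.** The strongest reply is that the article never says incomplete participants are dropped. The name is also used for mixed or likelihood repeated measures models, which keep them. Model form and missing-data rules are commonly left to an analysis plan, and that plan is not shown here. This stands. A reader might infer that the planned analysis is definitely a completers analysis, but the text supports only the conditional statement.

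The 20% is an allowance in the sample size, not a rule on who is analysed, and inflating for loss is compatible with either form. This also stands. The count of 115 is what would follow if loss reached that level.

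A reader might further infer that the completers' result would favour training. The documents do not support this. They give no reasons for loss and no rates by group. Outcomes come from an emailed questionnaire, so stopping training is not the same as being lost. The reference group could equally be the one that disengages. The illustrations above go against training, or show no bias, depending on what is assumed.

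The likelihood alternative is not automatically safe either. Step 4 shows it can be biased when a score that drives loss is left out. If baseline is entered only as a covariate, participants with nothing but a baseline score drop out of the mixed model just as they do from the ANOVA. These objections shape the fix but do not remove the point. One phrase covers two analyses that can give different answers, and its classical meaning does not deliver the stated principle.

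**Conclusion.** The concern holds in conditional form. In its classical form, the one method named does not fit the intention-to-treat commitment once week-20 scores are missing. At the 20% loss allowed for, about 115 of 573 randomised people would not contribute, and the estimate would be unadjusted change in completers.

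The size and direction of any bias are unknown. Under the assumptions in step 3 it is 0.09 to 0.24 points, or 10% to 27% of a 0.9-point target (0.09 / 0.9 and 0.24 / 0.9). Under other assumptions it is zero or of opposite sign. These figures show that the choice of form can matter. They do not predict what will happen in this trial.

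**What to change.** Replace the phrase naming repeated measures ANOVA with a likelihood-based linear mixed model for pain, specified as follows.

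- **Population:** all randomised participants with any pain score, in the group to which their cluster was randomised.
- **Outcomes:** baseline and all follow-up pain scores as repeated outcomes, including any collected mid-trial. Constrain the baseline mean to be common across groups. This keeps baseline-only participants in the model, although they add no direct week-20 information.
- **Terms:** group-by-time, stratum as a fixed effect, and random effects for cluster and person. These match the randomisation of clusters within 13 strata.
- **Assumption:** state that the analysis relies on data being missing at random given the modelled data.
- **Sensitivity:** add a delta-shifted analysis in which unobserved week-20 pain is made progressively worse, with shifts allowed to differ by group.
- **If multiple imputation is used:** training-diary attendance can enter only in the training groups, because the reference group does not train.

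The cost is a few sentences and a little more programming, with no change to conduct or data collection. The downside is reliance on missing at random, which the data cannot confirm and which the delta shift probes.
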